### 2.2. Secondary objectives

*a. To develop a rehabilitation program for VI recipients*

It is expected that patients will benefit from physiotherapeutic rehabilitation during prolonged VI stimulation by improving its functional outcome.

*b. To evaluate the interaction between vestibular and cochlear nerve stimulation*

It is expected that there will be interaction between the stimulation of the vestibular organ and the cochlea. The extent and clinical relevance will be characterized.

*c. To evaluate acute VI performance across several years*

It is expected that the CVI will induce stable VOR responses during acute stimulation over time. The clinical follow-up of the implanted patients will bring new insights for future research.

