| Time       | 08:00 | Breakfast                        |                                  | Breakfast                                   | Breakfast                                  | Breakfast |
| 09:00      |       |                                  |                                  |                                             |                                            |           |
| 10:00      |       | Costas array-based experiment    | CI and CVI aided DVA             |                                             | Static CI aided CNC + SPIN                 |           |
| 11:00      |       | First fitting - First SCC (1/2)  | First fitting - Third SCC (1/2)  | Second fitting - Second SCC (1/2)           | Combined fitting evaluation and adjustment |           |
| 12:00      |       | Break                            | Break                            | Break                                       | Break                                      |           |
| 13:00      |       | First fitting - First SCC (2/2)  | First fitting - Third SCC (2/2)  | Second fitting - Second SCC (2/2)           | Combined fitting evaluation and adjustment |           |
| 14:00      |       | Lunch                            | Lunch                            | Lunch                                       | Lunch                                      |           |
| 15:00      |       | First fitting - Second SCC (1/2) | Second fitting - first SCC (1/2) | Second fitting - Third SCC (1/2)            | Combined fitting evaluation and adjustment |           |
| 16:00      |       | Break                            | Break                            | Break                                       | Break                                      |           |
| 17:00      |       | First fitting - Second SCC (2/2) | Second fitting - first SCC (2/2) | Second fitting - Third SCC (2/2)            | Costas array-based experiment              |           |
| 18:00      |       | VBR                              | Semi-structured interview        | Familiarization with gait and balance tests | Final overall fitting check                |           |
| 19:00      |       |                                  |                                  |                                             | Static CVI aided CNC + SPIN                |           |

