#### 6.4.2. *Risks related to the AMP*

The AMP is a research use only device designed to allow simultaneous stimulation of the SCCs and the cochlea. It will be used under supervision of medical personnel while the patient is free to move around and perform routine daily activities. The audio processor part of the AMP is equivalent to a standard CI processor. The motion processor is added onto this, following the same design principles and stimulation restrictions as a CI processor to ensure safe stimulation of the CVI implant. To perform the fitting for the motion-processing part of the AMP, the AmpFIT software package is used, specifically designed to work together with the AMP.

This will be the first time the AMP will be used to drive a CVI implant in humans. To minimize any potential risks, the AMP will only be used by the patient when the patient is under supervision inside the hospital. Also, the patient is able to stop the stimulation of the CVI implant by the AMP at any point by turning it off or taking off the device. This immediately stops any current from passing through the CVI implant.

A more detailed description of the device related risks can be found in section D of the standard research file (the IMDD).

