|           |                       | 1b | Safety                        | stim. weeks                                          | Sec.               |      | Questionnaires, Interviews                                      |
|           |                       |    |                               |                                                      |                    |      | (S)AE's                                                         |
|           |                       | 1c | Efficacy of 3 stim. types     | VI-ON (week 1) vs VI-ON (week 2) vs VI-ON (week 3)   | Prim.              | Main | DVA                                                             |
|           |                       |    |                               |                                                      |                    | Aux. | fHIT, 3D HIT, Torsion Swing, Gait analysis, Perception platform |
| Secondary | Rehab.                | 2a | Rehab. program                | stim. weeks                                          | Prim.              |      | Gait analysis                                                   |
|           |                       |    |                               |                                                      | Sec.               |      | Questionnaires, Interviews                                      |
|           | CI                    | 2b | Interaction between CI and VI | CI-ON/VI-OFF (baseline) vs CI-ON/VI-ON (stim. weeks) | Prim.              |      | Aided CNC, SPIN, vestibular test                                |
|           |                       |    | CI as part of VCI             | CI-ON (up to 5 years)                                | Sec.               |      | Questionnaires, Interviews                                      |
|           | Long term             | 2c | Acute efficacy                | VI-ON (up to 5 years)                                | Prim.              |      | Subset of vestibular tests                                      |
|           |                       |    |                               |                                                      |                    |      |                                                                 |

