general result on the efficacy of prolonged vestibular stimulation. A further statement of CVI efficacy will be made based on the response to stimulation throughout the different prolonged stimulation weeks. Therefore the VOR tests will be performed several times during the prolonged stimulation weeks. A comparison of these results will yield statements on potential adaptation effects (e.g. habituation to receiving information via the CVI, increase/decrease in response gain and potential increase in VOR alignment). The same set of VOR and VSR tests measured throughout the prolonged stimulation weeks will also serve as parameters for comparing the different stimulation algorithms.

A subset of the vestibular tests will be performed during the annual follow-up visits. These parameters will be used to quantify the stability of acute stimulation and implant functionality over a clinical follow-up period of 5 years.

The functionality of the CI-part of the CVI will be assessed with an aided consonant-nucleus-consonant (CNC) hearing test. This will be done by making the comparison between aided CNC scores using the regular CI processor and aided CNC scores using the CVI processor (the AMP) with both CI and VI part active. During the CI follow-up visits speech in noise (SPIN) tests will be performed as part of the auditory follow-up test set to allow for evaluation of the CI part of the CVI implant and compare this outcome with CI performance of a regular CI implant.

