### ***CI rehabilitation***

CI rehabilitation will be performed as standard in our clinic. This includes a minimum of 11 visits (can be individually extended if necessary) in the time-span of 3 months to establish a fitting and to train the patient with using their CI. The CI rehabilitation period starts around 1 month after implantation. During the first visit a first fitting will be established and the patient will receive their standard CI processor (described in chapter 7), which will be connected to the CVI implant.

Each of the CI rehabilitation visits will take between 1 and 2 hours. During each CI visit, the impedances of all VCI electrodes will be checked. On top of that a short functional test of the VI electrodes will be introduced. This functional VI test will first be piloted in one subject. If the procedure is accepted, the intention is to repeat this functional VI test for each of the upcoming subjects as an extended part (max 60 min.) to three of the regular CI visits. This functional VI test will entail a short, maximum 2 seconds, stimulation of the VI electrode in each of the SSC, starting low in amplitude and increasing in small steps. To generate this stimulation the CI fitting software Maestro will be used. After each stimulation the patient will be asked if they felt something, what they felt and if it is comfortable. As soon as the patient experiences the stimulation as uncomfortable, the test will be stopped. Aside from the subjective feedback, also the eye movements will be captured objectively using video goggles. At no time during this function VI test, or any other moment during CI rehabilitation, the AMP processor will be turned on. The only time patients will actively use the AMP processor is during the VI fitting period and the prolonged stimulation period while they are being supervised in the hospital by the research team.

The final CI fitting visit, 3 months after the start of the CI rehabilitation period will include extra trial related procedures in addition to regular CI procedures. At this point ART measurement will be performed. Also cervical and ocular VEMPs are measured, if they were not absent during inclusion. Alongside this a SPIN hearing test is performed and the patient is asked to fill in questionnaires.

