### ***Baseline testing***

In the period of 6 to 24 months after the start of the CI rehabilitation the baseline testing and the prolonged stimulation period will be conducted. The full schedule of the baseline testing day can be found in chapter 3, table 3. The CI and VI fitting will be completed for all patients before the first patient starts with the baseline testing and prolonged stimulation (see chapter 3.2 and 10.4). The maximum time period between baseline testing and prolonged stimulation will be kept short (in the order of a few months) to ensure that the results from baseline testing serve as a good control for the prolonged stimulation period.

During the baseline testing day, the control measurements (VI-OFF) will be conducted for all vestibular outcome parameters. This includes the DVA, 3D HIT, fHIT, torsion swing, perception platform and gait and balance tests. The 3D HIT, fHIT and torsion swing tests are performed twice in a row: Once with an active CI and once without. This way the potential influence of CI stimulation on vestibular function and vice versa can also be characterized. Alongside the vestibular tests, an aided CNC hearing test with the regular CI processor will also be conducted.

The patient will also be asked to fill in a set of questionnaires at home and bring them to the hospital during the baseline testing day. At the end of the day the patient will be asked to fill in the VAS-based list of questions.

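### The hearing contrast for objective 2b changes the sound processor and the vestibular stimulation together, so it estimates their combined effect rather than vestibular-cochlear interaction

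*Protocol*

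**What the plan says.** Section 2.2 states the hypothesis for objective 2b: "It is expected that there will be interaction between the stimulation of the vestibular organ and the cochlea". Its extent and clinical relevance are to be characterised.

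The contrast is fixed in three places:

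- Table 6, row 2b, gives the measurement points as "CI-ON/VI-OFF (baseline) vs CI-ON/VI-ON (stim. weeks") and lists aided CNC, SPIN and vestibular testing as outcomes.
- Section 8.1.1 sets a "comparison between aided CNC scores using the regular CI processor and aided CNC scores using the CVI processor (the AMP"), the second condition being "aided CNC scores using the CVI processor (the AMP) with both CI and VI part active".
- Section 8.3.6, Baseline testing, says that "an aided CNC hearing test with the regular CI processor will also be conducted".

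On when the AMP is worn, Section 8.3.6, CI rehabilitation, says: "The only time patients will actively use the AMP processor is during the VI fitting period and the prolonged stimulation period". The baseline day is in neither period.

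Two statements bear on whether the processors can be treated as interchangeable. Both are in Section 6.4.2. One describes the audio part of the AMP as equivalent to a standard CI processor. The other reads: "This will be the first time the AMP will be used to drive a CVI implant in humans".

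**The concern.** The comparison is meant to show what vestibular stimulation does to hearing, but its two conditions also differ in the device that delivers the sound. One is the processor that patients have trained on and worn every day. The other is a research processor worn only in supervised sessions.

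A lower CNC score in the stimulation weeks could be reported as interaction or current spread when part or all of it comes from the processor. An advantage of the AMP could equally hide a real interaction. No analysis plan can repair this afterwards, because separating the two effects needs a condition that has to be measured.

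**Working it through.** The documents give no figure for objective 2b, so there is none to reproduce. The check is whether the planned conditions can identify the effect of interest.

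**Conditions in the Table 6 hearing contrast**

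| Condition | Processor | VI | Source |
|---|---|---|---|
| Baseline, static and dynamic CNC | Regular | Off | Table 2; Section 8.3.6, Baseline testing |
| Thursday of each stimulation week, dynamic CNC | AMP | On | Table 4; Section 8.1.1 |

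**Model.** Let P = 1 for the AMP and V = 1 for VI on, and write the expected score as μ + πP + νV. Here π is the processor effect and ν the effect of vestibular stimulation.

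- Regular processor, VI off: μ
- AMP, VI on: μ + π + ν
- Planned difference: π + ν

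The condition matrix has rows (1, 0, 0) and (1, 1, 1), so its rank is 2 for 3 parameters. Only the sum π + ν can be estimated. If ν = 0 and π = −k, the contrast shows a loss of k that is not interaction. If π = +k and ν = −k, the contrast is zero although interaction exists.

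**Do the three algorithms help?** Add one term for modulation and one for reduced baseline. There are then four conditions (regular processor, plus three algorithms on the AMP) and 5 parameters. The rank is 4. The modulation and baseline-level terms can be estimated, because they are compared within the AMP with the VI on. The processor and VI on/off terms stay tied together.

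**With one added condition.** AMP with VI off has expected score μ + π and row (1, 1, 0). The rank becomes 3 of 3:

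- AMP/VI-on minus AMP/VI-off = ν
- AMP/VI-off minus regular/VI-off = π

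The planned contrast also spans the time from the baseline day to the stimulation weeks, which Section 8.3.6 puts in the order of a few months. A same-day AMP pair removes that difference too.

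**Is an AMP/VI-off test already planned?** The relevant places, side by side:

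- Table 3, fitting day 4, 10:00, lists "Static CI aided CNC + SPIN" and names no processor. A CVI-aided version follows at 19:00.
- Section 5.1.1 says that patients use the experimental processor during VI testing periods, which would put the 10:00 test on the AMP.
- Section 8.1.1 pairs CI-aided hearing with the regular processor, which would put it there instead.
- Section 8.3.2 defines static CNC as a test without vestibular stimulation, which would make even the CVI-aided static test a VI-off test.
- Section 8.3.6, VI fitting, describes the fitting-period hearing test as run with vestibular and cochlear electrodes both active.

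These do not settle the processor and VI state of either day-4 test. Nor does Table 6 draw the 2b contrast from the fitting week. In the example schedules for baseline and the stimulation weeks, the only hearing test on the AMP is dynamic CNC with the VI on. Table 1 is illegible in the copy reviewed, so its entries could not be checked.

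**The case against.** The strongest reply is the equivalence statement in Section 6.4.2. If the AMP's audio part performed exactly like the regular processor, and familiarity made no difference, π would be zero and the contrast would be clean. Familiarity is also less of a problem than it first appears. By Thursday the patient has used the AMP in the fitting period and for several days at about 8 hours a day. This stands as a reason to expect π to be small. It does not show that π is zero: equivalence is asserted in a risk section, without hearing data, for a device in first human use with this implant, and no check is planned. The device dossier that the section refers to was not available for this review.

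A second reply is that own processor against combined device is a legitimate practical question. Section 8.1.1 introduces the comparison as an assessment of the functionality of the CI part, and Section 1.4.6 wants performance in clinically relevant use. That also stands. The difficulty is only that Table 6 uses the same comparison to answer the interaction question.

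A reader might infer that the design never measures hearing on the AMP with the VI off. The documents do not support that much. The day-4 slot names no processor, and Section 4.4 envisages the VI part inactive while the CI stays active.

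A reader might also infer that objective 2b cannot be answered at all. That goes too far. Table 6 includes vestibular tests under 2b, and 3D HIT, fHIT and torsion swing are run at baseline with and without an active CI. The ART measurements in Section 8.3.3 give evidence on current spread, and CNC differences between algorithms on the AMP are free of the processor effect.

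**Conclusion.** The point holds for the hearing outcomes of secondary objective 2b. As stated in Section 8.1.1 and Table 6, a CNC difference estimates processor effect plus VI effect, and no AMP/VI-off hearing test is clearly specified that would separate them.

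The size of the bias equals the processor effect. The documents give no value for it, and neither its sign nor its magnitude should be presumed. The rank argument assumes additive effects of processor and VI. Without additivity the planned pair is no more informative.

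The consequence is limited. This is one outcome family of a secondary objective in a trial that Section 10 calls exploratory, and the DVA comparison is untouched. It is still worth correcting before testing starts, because the correction is cheap and cannot be made from the data later.

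**What to change.** 1. Make AMP with CI on and VI off the reference for the 2b hearing contrast. Add one list in that mode to the Thursday dynamic CNC in each stimulation week, with the order of the VI-on and VI-off lists set in advance. This is the step that repairs the Table 6 contrast, since that contrast is dynamic.
2. Specify the same mode for the 10:00 CI-aided CNC and SPIN slot on fitting day 4, paired with the 19:00 CVI-aided test. Note in the text that combined fitting adjustment falls between the two. This static pair supports step 1 but does not replace it.
3. Keep the regular-processor baseline as a separate comparison of devices.
4. State the processor and the VI state for every hearing test, and reconcile Table 3 with Sections 5.1.1, 8.3.2 and 8.3.6.
5. Amend Section 8.1.1 and Table 6, row 2b, to match.

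The cost is a few minutes per stimulation week: three extra lists per patient, or 3 × 8 = 24 to 3 × 13 = 39 lists over the trial. If the day-4 slot is currently meant for the regular processor, a same-day comparison with that processor is lost, although the baseline-day CNC on it remains.

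All of this assumes that the AMP can run with its vestibular part off. If it cannot, the protocol should say that the contrast measures the combined effect of processor and VI, and the result should not be reported as interaction.

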#### 8.1.2. *Secondary study parameters/endpoints*

The patients' subjective experience with the CVI will be quantified using both questionnaires and a number of semi-structured interviews at different points during the study duration. An overview of the time points at which questionnaires and interviews will be administered can be found in table 1, 2, 3 and 4 (chapter 3) and chapter 8.3. The results of these questionnaires and interviews will allow us to more extensively describe our patient population, quantify the impact that both the CI and the VI functionality have on patient well-being, characterize the perceived benefit the CVI will pose to the patient and allow us to see if the CVI meets the patients' expectations. All this data will also be vital for creating a health technology assessment (HTA), which will aid the further development of the concept of vestibular stimulation.

Previous research within our group (partly as-of-yet unpublished) has shown the diversity of reported symptoms among BV patients. These previous interview studies have shown the importance of characterizing all the different subjective aspects and processes on which the CVI can have an effect. Alongside this, based on clinical experience during the previous VI trial in Maastricht, the patients which are eligible for inclusion into the trial have a personal drive to share their story and give their opinion. Therefore, we wish to channel this drive into quantifiable results by using an elaborate set of subjective outcome measures. The questionnaires and interviews will be spread out over the full trial duration, and across several days during the stimulation weeks, to reduce the burden on the patient

All questionnaires are described in chapter 8.3.5 and can be found in section F1 of the standard research file.

## 8.2. Randomization, blinding and treatment allocation

During the implantation, CI fitting, VI fitting and baseline testing the researchers and patients will not be blinded since these procedures will be identical for all patients. However, during the prolonged stimulation period patients will be blinded to which type of stimulation algorithm is used. The three types that will be tested will each be randomly assigned to one of three 4-day prolonged stimulation periods. This way the effect of different stimulation algorithms can be assessed both within patients and between patients.

The sequence of stimulation algorithms will be randomized and single-blinded. Randomization will be performed by using a block randomization-based design. Since there are 3 stimulation algorithms which will be randomized over 3 time periods, each algorithm appearing only once, there are 6 distinct algorithm sequences. To equally distribute all the patients over 6 algorithm sequences a block size of 6 is used. A custom “urn” will be created in the following way: Each of the 6 possible algorithm sequences is added to the urn once. Additional algorithm sequences are chosen at random without replacement from the total of 6 algorithm sequences and also added to the urn. This is done until the amount of algorithm sequences in the urn is equal to the amount of patients which will be included. The urn now contains as many allocation possibilities as there are patients, with each allocation possibility featuring at least once and no more than twice. Randomization will be performed in the period after VI fitting and before the prolonged stimulation period. When an allocation is assigned to a patient during randomization, this allocation is removed from the urn. Therefore, the urn will be empty after all patients have been allocated. This way all possible algorithm sequences will be allocated to at least one patient without offering predictability of algorithm sequence allocation at any moment.

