#### 3.1. Study design rationale

The study will be conducted with a cross-over design. Previous VI research has shown large variations between patients. For accurate assessments of the efficacy of different stimulation algorithms a within patient comparison is most suitable. Carry-over of stimulation effects are expected to be minimal based on previous experience with VI patients which showed repeatable results of acute stimulation with as little as one day of wash-out in between. Within this study design, the resting period between the different stimulation periods is chosen to be three days to decrease the burden on the patient and to further decrease the chance of carry-over.

Previous experience with vestibular stimulation has shown that the difference between stimulation on or off will be clearly noticeable by both the patients and the examiners. Therefore blinding the patient on whether or not they receive stimulation is unwarranted. To reduce further patient-induced bias, the patients will be blinded as to which stimulation algorithm is used in which week. Effort will be made to keep the bias induced by the researchers who conduct the examinations and the data analysis to a minimum. However, the current study set-up in combination with the current capabilities of the research device and fitting software do not allow for a fully double-blinded trial.

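### Section 8.2 claims sequence allocation is never predictable, but if the urn is drawn patient by patient until empty, later sequences can be guessed well above chance

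*Protocol*

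**What the plan says.** Section 8.2 randomises the order of the three stimulation algorithms. It counts the possible orders ("there are 6 distinct algorithm sequences") and builds an urn in two parts. For the fixed part, "Each of the 6 possible algorithm sequences is added to the urn once". For the random part, "Additional algorithm sequences are chosen at random without replacement from the total of 6 algorithm sequences and also added to the urn", until the urn holds as many sequences as there are patients. Each sequence is then present once or twice. An assigned sequence is taken out: "Therefore, the urn will be empty after all patients have been allocated". The section concludes that every sequence is used at least once "without offering predictability of algorithm sequence allocation at any moment".

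Four other statements bear on this:

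- Section 4.4 gives a sample size of 8 to 13. The inclusion text in section 8.3.6 says 8.
- Section 8.2 blinds patients only. Section 3.1 says the set-up and the device software "do not allow for a fully double-blinded trial".
- Section 8.2 places randomisation after VI fitting and before prolonged stimulation. It does not say whether all sequences are drawn in one session or one patient at a time, nor who fills and holds the urn.
- The baseline testing text in section 8.3.6 says: "The CI and VI fitting will be completed for all patients before the first patient starts with the baseline testing and prolonged stimulation". Section 3.2 allows 18 months for baseline testing and stimulation.

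**The concern.** An urn that holds exactly one sequence per patient and is emptied without replacement cannot give independent draws. Every sequence removed changes what can come next, so anyone who knows the earlier draws can guess the later ones better than 1 in 6. Unpredictability at every moment is the property that this mechanism lacks.

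Sequence order is the only randomised element of the trial and supports the algorithm comparison (objective 1c). Order could matter by the protocol's own account: section 1.4.3 expects adaptation in the first weeks of stimulation, and section 8.3.6 tests for a learning effect on the perception platform. If someone who knows earlier draws also influences which patient starts next, a patient expected to tolerate stimulation poorly or to learn quickly could be matched to a preferred order. The protocol does not say that this would happen. Its claim of unpredictability would lead a reader to think that it could not.

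**Working it through.** **Inputs.** Number of sequences: 3! = 6, as section 8.2 states. Urn size: N. Extra sequences: N − 6, all different. Doubled sequences are therefore N − 6 in number, and single ones 6 − (N − 6) = 12 − N. For N = 8 to 12 this gives one or two copies of each sequence, which reproduces the protocol's statement. N = 13 is left out because it would need 7 extras from 6 sequences, so the urn cannot be built as described.

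**Benchmark.** With an unpredictable draw, each guess is right with probability 1/6, so N/6 correct guesses are expected (8/6 = 1.33; 12/6 = 2.00).

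**Case A: earlier draws and urn contents known.** The best guess is a sequence with most copies left, divided by the sequences remaining.

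- N = 8, draw 1: 2/8 = 0.25.
- Draw 2: a doubled sequence is still complete whatever came first, so 2/7 = 0.286.
- Continuing exactly over all paths, the mean best-guess probabilities are 0.250, 0.286, 0.310, 0.329, 0.354, 0.405, 0.536, 1.000. They sum to 3.47.
- The last draw is certain at every N.

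**Case B: earlier draws known, extras hidden.** The guesser updates on which sequences are doubled.

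- N = 8, draw 1: 1/6 = 0.167, exactly chance.
- Draw 2: the sequence just drawn is doubled with probability (2/6 × 2) / (2/6 × 2 + 4/6 × 1) = 0.5, so it recurs with probability 0.5 × 1/7 = 1/14. Each of the other five has probability (1 − 1/14)/5 = 0.186, already above 1/6.
- All eight draws: 0.167, 0.186, 0.211, 0.245, 0.296, 0.381, 0.488, 0.600. They sum to 2.57.

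**Last draw in case B.** There are two possibilities.

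- The remaining sequence is a single one, with probability (12 − N)/N. It is then the only sequence not yet seen, and so it is certain.
- Otherwise it is the second copy of a doubled sequence and could be any of the 13 − N sequences seen once. At N = 8 that is 5 candidates. At N = 12 it is 1, so the last draw is again certain.

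Check at N = 8: 4/8 × 1 + 4/8 × 1/5 = 0.60, which agrees with the list above.

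| N | Chance, N/6 | Correct guesses, contents known | Correct guesses, extras hidden | Last draw certain, extras hidden |
|---|---|---|---|---|
| 8 | 1.33 | 3.47 | 2.57 | 4/8 = 0.50 |
| 9 | 1.50 | 3.75 | 2.70 | 3/9 = 0.33 |
| 10 | 1.67 | 3.97 | 2.92 | 2/10 = 0.20 |
| 11 | 1.83 | 4.16 | 3.33 | 1/11 = 0.09 |
| 12 | 2.00 | 4.33 | 4.33 | 1.00 |

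At N = 12 every sequence is in the urn twice, so hiding the extras hides nothing.

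**The case against.** The strongest reply is that the protocol nowhere states that draws are made one patient at a time. All patients are to be fitted before any starts, and randomisation falls after fitting, so a single drawing session fits the text equally well. Prediction from earlier draws would then have no role. This stands, and the finding is conditional on it. It does not rescue the sentence, which claims unpredictability at every moment without saying that the draw is made once.

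Second, a reader might infer that the last sequence is always certain. The documents do not support that. Certainty at every N needs known urn contents, and section 8.2 does not say that the team sees the extras. With extras hidden, certainty falls from 50% at N = 8 to 9% at N = 11, and returns to 100% only at N = 12.

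Third, a reader might infer that steering one patient shifts the mix of algorithms across weeks. It cannot. The urn fixes how often each sequence occurs and all of it is used, so scheduling order changes only who receives which sequence.

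Fourth, the practical effect is small. Everyone is already implanted and fitted, so selection into the trial is not at risk. Each patient is planned to receive all three algorithms. Section 10.1 compares algorithms by descriptive statistics only, and section 10 calls the trial exploratory. All of this stands and limits the weight of the point. Who holds the list may be settled in a document not shown here, so silence on custody is not counted as an error.

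**Conclusion.** The claim of no predictability is wrong for N = 8 to 12 if sequences are drawn patient by patient and earlier draws are known to the team. Above-chance guessing then begins at the second draw at the latest. Expected correct guesses at N = 8 are 2.6 with extras hidden and 3.5 with contents known, against 1.3 by chance. At N = 12 they are 4.3 against 2.0 in either case.

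The result rests on two assumptions that the protocol neither states nor excludes: sequential drawing, and knowledge of earlier sequences. The second is plausible, since blinding covers patients only, but section 3.1 says no more than that full double-blinding is not possible. Staggered starts are likely, given the 18-month window and the reference in section 10.4 to results from the first patients' stimulation periods. That does not show that the draws themselves are staggered.

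What is at stake is the matching of patients to sequences in the descriptive comparison under 1c. The sequence counts are not affected, and the VI-OFF versus VI-ON comparison does not rest on sequence. The correction is worth making because the statement is false under a natural reading and the remedy is nearly free.

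**What to change.** In section 8.2, delete the no-predictability claim or limit it to what the procedure delivers. Then state that:

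- once all patients are fitted and N is known, all sequences are assigned to patient codes in one step, before the first patient starts;
- this is done by someone not involved in testing or scheduling, for example the trial centre that already monitors the study under section 12.2;
- each patient's sequence is released only after that patient's baseline day.

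The balance of sequences is unchanged. The team could still guess some late sequences from those already released, which is why the claim itself has to go. Changing the order of patients could no longer change who receives which sequence.

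The cost is a few sentences and one list that must be prepared and held outside the testing team. No patients, visits or tests are added, and nothing is proposed about how or when stimulation settings are fixed.
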